#### Development of data collection tools and their validation

The data collection tools will be developed by public health experts based on a review of available literature, standard treatment guidelines for snakebite, and consultation with the TAC.

*Retrospective and Prospective data form*. These two data collection forms will include questions about the basic demographic characteristics of the snakebite victim followed by details of the event of snakebite, signs and symptoms, first aid, and steps taken for the management including usage of anti-venom. The forms will have a separate ‘Follow Up’ section for transferred out patients. Hospital records will be used for form filling.

*Facility Survey Questionnaires*. Separate questionnaires will be developed for Primary Health Centre (PHC), Rural Hospital (RH) / Community Health Centers (CHC), and Sub District Hospital (SDH) / District Hospital (DH) to document staff positions, drugs, equipment, anti-venom availability and utilization, infrastructure, laboratory investigations, and Information Education Communication (IEC) materials and activities. The questionnaires will concur with the Indian Public Health Standards (IPHS) Guidelines and STG, 2017 for respective facilities.

*Focused Group Discussion (FGD) Guide*. The FGD guide will consist of open-ended, semi-structured questions to elicit the knowledge, awareness, and perceptions of people in the study area regarding snakes and snakebites, first aid, prevention methods, management, and health-seeking behavior. The FGD guide will be developed in English and later translated to local languages.

*Questionnaire for healthcare providers*. Separate questionnaires for peripheral workers and Medical Officers (MO) at facilities would be developed based on the STG, 2017 and WHO SEARO Guidelines for management of snakebites. They will try to capture the knowledge, perceptions, and experiences of healthcare providers regarding snakes and snake bites, anti-venom use, challenges encountered while managing snakebite cases at public health facilities.

All the developed tools will be validated through the following methods–

*Face Validity*. The TAC will critically review the tools to confirm that they have sufficient and pertinent information to gather the knowledge, awareness, and perceptions of the respondents. The panel will be asked to comment on the relevance, language, ease of understanding, and ability of the questions to elicit desired responses.

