#### Phase I–Retrospective data collection, facility surveys, and FGDs in the community

Two-year retrospective data (01 January 2020 to 31 December 2021) will be collected from all the public health facilities in study areas where snakebite management is expected to be provided. This includes all the Primary Health Centers, Rural Hospitals / Community Health Centers, Sub District Hospitals and District Hospitals. Medical Colleges where severe cases are referred from the study blocks will also be included to ensure quality retrospective data collection. Additional data on snakebite deaths will also be collected from local authorities, panchayat office, registrar of births and deaths so that maximum deaths are captured. A cross-sectional survey will assess the preparedness of the public health facilities for SBE management. Retrospective data and facility data will be collected and entered into an online application. The captured data will be verified at regular intervals by the study coordinator.

The qualitative component will involve conducting community FGDs in the study areas. Total 24 FGDs will be conducted, six per block (three male, three female). Each FGD will be restricted to 8 to 16 participants. Actual number of FGDs may vary according to the saturation of responses. FGDs will be conducted at common and acceptable community places. The Primary Health Centers (PHCs) in the block would be enlisted and one random village would be picked per PHC. The information about conduct of a FGD would be given to the villagers with the help of the frontline community healthcare workers and community leaders and 8–16 randomly selected participants would be invited to participate. Participants belonging to the community and above 18 years of age will be included for FGDs. Healthcare providers will be excluded.

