#### Phase III—Evaluation of the healthcare providers

Assessment of the basic knowledge, awareness, and perceptions on snakebite management and preventions among healthcare providers will be conducted. All the Medical Officers and Peripheral Health Workers from the study blocks who agree to participate will be included in the study. Each block will have approximately 40 MOs; so nearly 160 MOs will be assessed during the study. Similarly, around 600 peripheral workers (150 per block) will also be evaluated. Actual numbers may vary as the MOs or healthcare workers are frequently transferred in the health system.

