#### Phase V—Impact evaluation of interventions

FGDs will be conducted in the study areas to evaluate the post-intervention community knowledge with the same methodology as discussed in Phase I, two months after the educational intervention. Pre- and post-training evaluations will be done to assess knowledge retention and the impact of training on the healthcare providers. Prospective data will be collected from the health facilities after the capacity building training of Medical Officers in study blocks for a period of one year. Incidence and case fatality rate in the study blocks will be calculated based on the prospective data. The impact of capacity building on the healthcare system will be assessed by comparing prospective data with the retrospective (pre-intervention) data.

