### Statistical analysis

The baseline data will be analyzed separately for different strata (Gender-wise, Age-wise, seasonal variation, distribution of venomous and non-venomous snakebite, site of snakebites, and categorization of snakebite based on the sign and symptoms of envenomation). The differences across strata will be investigated using appropriate statistical tests based on the nature of the variables. The Chi square and Fisher’s Test would be used to compare categorical variables while the independent t-test would be used to compare continuous variables. To check the factors associated with the incidence of snakebite, bivariate regression models will be used and results will be presented through odds ratios. The primary outcome will be reduction in the incidence of snakebite cases per 100000 population and a reduction in the case fatality rate in the study areas at the end of two years, measured by comparing the pre- and post-intervention data on the incidence of snakebite and mortality in the four study blocks. The secondary outcomes will include reduction in mean bite to needle time, reduction in the proportion of snakebite victims referred to higher facilities for management, increase in the proportion of MOs providing treatment as per STG 2017, mean increase in the number of vials of anti-venom administered to victims, reduction in the proportion of cases with severe complications including reduced kidney failure and amputation rate. Data from interviews of healthcare providers will be analyzed further for frequency. A summative index will be developed from the knowledge test of health workers. Two sample t-test will be used to compare the change in the knowledge of Medical Officers and the healthcare workers after the training. A p-value < 0.05 will be considered statistically significant. All the quantitative data will be entered and analyzed using the statistical package SPSS (version 26.0; IBM Corporation, Armonk, NY, USA).

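### The guideline-adherence outcome counts Medical Officers, but treatment is recorded per patient over unequal windows; if built from the case forms, it depends on caseload

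*Protocol article*

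**What the plan says.** The Statistical analysis section lists among the secondary outcomes an "increase in the proportion of MOs providing treatment as per STG 2017". The denominator is therefore MOs.

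The section on data collection tools describes the retrospective and prospective forms by patient: "These two data collection forms will include questions about the basic demographic characteristics of the snakebite victim followed by details of the event of snakebite". They go on to cover signs, first aid and management, including anti-venom. On their source it says: "Hospital records will be used for form filling". It mentions no field for the treating MO. The separate MO questionnaire in the same section covers knowledge, perceptions and experiences, with anti-venom use and the difficulties met in managing cases.

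The windows differ. Phase I: "Two-year retrospective data (01 January 2020 to 31 December 2021) will be collected from all the public health facilities". Phase V has the prospective data "collected from the health facilities after the capacity building training of Medical Officers in study blocks for a period of one year". Phase V also states the comparison: "The impact of capacity building on the healthcare system will be assessed by comparing prospective data with the retrospective (pre-intervention) data".

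Phase III expects about 40 MOs per block, about 160 in all, and warns: "Actual numbers may vary as the MOs or healthcare workers are frequently transferred in the health system".

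**The concern.** Among the secondary outcomes, this is the one that names the Standard Treatment Guidelines (STG), whose implementation is the third objective. The outcomes listed beside it on referral, anti-venom vials and complications are counted or averaged over patients. This one alone is counted over MOs.

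To get from patient forms to a share of MOs, each MO must be classed from his or her own cases. That class depends on the number of cases as well as on how the MO treats. An MO observed for two years has about twice the cases of one observed for one year, so the same practice can give a different proportion before and after. MOs without a snakebite case cannot be classed, and their number also changes with the length of the window. A rise or fall could then be read as an effect of training when practice had not changed.

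**Working it through.** The article gives no sample size, baseline value or target for this outcome, so there is no figure to reproduce. Its only related arithmetic, 4 x 40 = 160 MOs, is consistent. The check asks how far the outcome moves when practice does not change.

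**Inputs from the protocol:** two-year baseline, one-year follow-up, about 160 MOs, significance at p < 0.05 (taken as two-sided).

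**Assumptions, not in the protocol:** cases per MO follow a Poisson distribution with mean m per year (m = 1, 2, 3, 5, 10). Each case is managed per STG with the same probability p in both periods (p = 0.3, 0.5, 0.7, 0.8, 0.9). No transfers at first. Only MOs with at least one case are counted.

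**Formulas.** Let L be the expected cases per MO in the window: L = 2m at baseline, L = m at follow-up.

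- All cases per STG: [exp(-L(1-p)) - exp(-L)] / [1 - exp(-L)]
- Any case per STG: [1 - exp(-Lp)] / [1 - exp(-L)]
- At least a share c of cases: sum over n of P(N = n | N >= 1) x P(Bin(n, p) >= cn)
- Patient-level proportion: p in both windows

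**Worked example**, all-cases rule, m = 3, p = 0.8:

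- Baseline, L = 6: (0.3012 - 0.0025) / 0.9975 = 29.9%
- Follow-up, L = 3: (0.5488 - 0.0498) / 0.9502 = 52.5%
- Shift: +22.6 points. With 160 MOs per period, the chance of p < 0.05 is about 0.99.

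**Selected results, practice unchanged:**

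| Rule for an MO | m | p | Baseline % | Follow-up % | Shift (points) |
|---|---|---|---|---|---|
| All cases | 1 | 0.8 | 61.9 | 71.3 | +9.5 |
| All cases | 5 | 0.9 | 36.8 | 60.4 | +23.6 |
| Any case | 3 | 0.3 | 83.7 | 62.5 | -21.2 |
| Any case | 2 | 0.5 | 88.1 | 73.1 | -15.0 |
| At least 80% | 3 | 0.8 | 58.0 | 60.2 | +2.2 |
| At least 80% | 2 | 0.5 | 15.9 | 27.7 | +11.8 |
| At least 80% | 10 | 0.9 | 92.5 | 86.5 | -6.0 |
| At least 50% | 3 | 0.8 | 96.3 | 92.2 | -4.1 |
| At least 50% | 5 | 0.3 | 13.0 | 24.5 | +11.5 |

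Over the whole grid, the two threshold rules together range from about -6 to +12 points. A strict-majority rule (more than 50%) mirrors the at-least-50% rule with p replaced by 1 - p and the sign reversed. For example, it gives -11.5 points at m = 5, p = 0.7.

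**MOs with no case.** The expected share is exp(-2m) at baseline and exp(-m) at follow-up. At m = 1 that is 13.5% against 36.8%; at m = 3 it is 0.2% against 5.0%.

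**Transfers.** Suppose a share t of posts changes hands between the two baseline years. Then 160(1 - t) MOs are seen for two years and 320t for one, so 160(1 + t) distinct MOs are counted. For t = 25% (120 + 80 = 200 MOs), all-cases rule, m = 3, p = 0.8:

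(120 x 0.9975 x 0.2995 + 80 x 0.9502 x 0.5252) / (120 x 0.9975 + 80 x 0.9502) = 75.8 / 195.7 = 38.7%

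The shift falls from +22.6 to +13.8 points. At t = 50% it is +7.8 (240 MOs), and at t = 100% it is 0 (320 MOs).

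**Patient as unit.** The expected change is 0 in every scenario. Only precision depends on the number of cases.

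**The case against.** The strongest reply is that the article never says this outcome comes from the case forms. The Abstract and the second objective speak of assessing providers' practices, the MO questionnaire touches on anti-venom use and on managing cases, and Phase V plans evaluations before and after training. Measured that way, a share of MOs has its natural unit and the window problem does not arise. The forms mention no link to a treating MO, which may favour that reading. A rule for classing an MO is also detail that an article may leave to the full protocol or the analysis plan.

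Much of this stands. The source is inferred, so the size of the artefact is conditional, and the absence of a rule is not itself the criticism. But the outcome is worded as treatment provided, and a questionnaire yields reported practice. Where the case data are used, the MO unit and the unequal windows are fixed in the article. A later rule would settle the size and direction of the artefact but would not in general remove it.

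A reader might infer stronger claims that the protocol does not support:

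- **A false fourfold rise.** With exactly 8 and 4 cases and p = 0.7, an all-cases rule gives 0.7^8 = 6% and 0.7^4 = 24%. The article states no such rule and no caseload. About 4 cases a year can be built from its figures. Block populations times state death rates give 431,095 x 3.5/100,000 + 210,520 x 6.7/100,000 = 15.1 + 14.1 = 29.2 deaths. Dividing by the 4.5% case fatality of one cited study gives about 649 bites, and 649/160 = 4.1. That is a community estimate, and the Introduction says most deaths occurred at home, so it is not MO workload.
- **A false fall of 16 points.** With the same 8 and 4 cases, a more-than-half rule gives 81% and 65%. This is largely an effect of ties: at least half gives 94.2% and 91.6%.
- **Transfers making it worse.** In the calculation, turnover within the baseline shrinks the window effect. What it does change is which MOs, and how many, are counted.

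**Conclusion.** The concern holds in conditional form. The outcome is counted over MOs, while the only described record of treatment given is per patient, and a two-year baseline is set against one year of follow-up.

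- **If it is derived from the case forms**, it depends on caseload and window length. With unchanged practice and an assumed 1 to 10 cases per MO per year, the shift can exceed 20 points upward (all cases) or downward (any case). It is about -6 to +12 points under the at-least-50% and at-least-80% rules. Turnover can reduce it, and MOs without a case drop out.
- **If it is taken from the MO questionnaire**, the window artefact is absent, but the outcome is reported practice.

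The sizes rest on Poisson caseloads, a constant p across MOs and periods, and classing rules that the article does not state. This is a secondary outcome, so the primary comparison is not affected. The change is still worth making, because the alternative is cheap and free of the artefact.

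**What to change.** Redefine the outcome as the proportion of snakebite patients managed per STG 2017. Score it with one checklist applied in the same way to the retrospective and prospective forms and restricted to items available in both. Analyse it at patient level with facility as the cluster. Report MO questionnaire results separately, labelled as knowledge or reported practice.

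The cost is a change of outcome wording and one scoring sheet, using forms already planned. The downside is that the 2020-2021 hospital records may lack some STG items. The checklist may then be shorter than a purely prospective one, and missing items should be reported by period.

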## Abstract

**Background:**

Snakebite envenoming (SBE) is an acute, life-threatening emergency in tropical and subtropical countries. It is an occupational hazard and a major socioeconomic determinant. Limited awareness, superstitions, lack of trained health providers, poor utilization of anti-venom results in high mortality and morbidity. India is the snakebite capital of the world. Yet, information on awareness, knowledge, and perceptions about snakebite is limited. Data on capacity building of health systems and its potential impact is lacking. Recommended by the National Task Force on snakebite research in India, this protocol describes the National Snakebite Project aiming for capacity building of health systems on prevention and management of snakebite envenomation in Maharashtra and Odisha states.

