SBE burden coupled with a lack of awareness amongst the Medical Officers (MOs) and other healthcare providers about the National Snakebite Management Protocol (2009) and Standard Treatment Guidelines (STG, 2017) creates major hurdles in management of SBE [13]. An irrational usage of anti-venom skin test was also reported in the tribal block of Dahanu, Maharashtra [17]. Primary Health Centers in rural India face a multitude of problems including the acute shortage of trained human resources, unavailability of anti-venom and emergency ventilation services [18]. Issues with public health facilities and geographical inaccessibility supplemented by superstitions and cultural beliefs regarding snakes force SBE victims to seek care from faith healers [19, 20]. Studies in rural and tribal areas have revealed inadequate knowledge about venomous snake identification and faith healers were the first choice for about 38–68% of people for SBE management [17, 21–24]. Most of the traditional and herbal methods of first aid and management of snakebite have been found to cause more harm than benefit [25, 26]. Proper knowledge of snakes and snake-bite management was also found to be either diminutive or absent in the majority of participants as reported by a study from Haryana [27]. Fear, negativity, and unfamiliarity regarding prevention and ambivalent opinions on health-seeking are known drivers of people’s perception of snakes and snakebites [28]. These findings strongly suggest the need for community awareness on the prevention and first aid of snakebite and empowerment of frontline healthcare workers and Medical Officers for effective management of SBE in public healthcare settings.

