## Materials and methods

### Study scheme

The interventional study has retrospective, prospective, cross-sectional, and qualitative components and will be conducted in a community as well as hospital settings (Fig 1). It is divided into five phases (Fig 2). Phase I involves collecting retrospective data of snakebites, facility surveys, and focus group discussions (FGDs) in the community. Phase II is to increase awareness and empower the community on prevention, first aid, and early transport of snakebite patients to the nearest health facility. Phase III will be to evaluate the basic knowledge on snakebite management and anti-venom utilization among healthcare providers. Phase IV is to empower the health system for management of SBE and optimal utilization of anti-venoms through training programs and Phase V will focus on the impact evaluation of the health system and community interventions using FGDs and comparison of pre-and post-intervention data.

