## Discussion

SBE remains a major public health hazard predominantly in tropical countries [3]. In Asia up to two million people are bitten by snakes every year; the majority of them are women, children, and poor rural communities [32]. SBE has highly effective treatment and severe complications can be prevented with a correct dose of anti-venom [33]. Snakebite treatment remains a complex issue in countries like India due to various factors—poor community knowledge, ill-equipped hospitals, treatment accessibility, travel time, and reliance on faith healers for treatment [34]. Very little attention is drawn towards the assessment of basic knowledge of medical doctors on management of snakebite and its complications [35, 36].

A study conducted in India and Pakistan concluded that standard protocols and training are required to empower doctors to reduce snakebite mortality [35]. Another study from Bangladesh revealed that peripheral healthcare workers lack knowledge, experience, and adequate skills required to treat snakebite victims [37]. In a recent study from Bhutan, only 25% of health workers had adequate knowledge of snakebite management. However, 63% of medical doctors were found to have adequate knowledge compared to other healthcare workers [23]. A study in Haryana on farmers, teachers, medical residents, and students reported that only 13% participants, were aware of the ‘big four’ snakes [27]. Lack of appropriate knowledge on snakes, first aid, treatment, and prevention among the clinicians was also reported in northern Nigeria [38]. In Hong Kong, only 29% of clinicians were confident about treating snake bites [36].

India is a major manufacturer of anti-venoms. However, there is a paucity of satisfactory data regarding the number of anti-venom vials needed to reverse the clinical effects of SBE [39]. Passivity, inaction and supply-demand incoordination have resulted in both unavailability and inadequacy of anti-venom marginalizing the effective cure to SBE [40]. A study in Africa reported that compared to requirements, the number of effective treatments available for SBE might be as little as 2.5% [41]. In many African and Asian countries, anti-venom production is either at standstill or stopped altogether [42].

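### The vial-count secondary outcome treats more anti-venom as the favourable result without reference to envenomation or correct dose, so on its own it cannot show progress toward optimal use

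*Protocol article*

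**What the plan says.** The Statistical analysis section of the protocol article lists, among the secondary outcomes, a "mean increase in the number of vials of anti-venom administered to victims". The direction is part of the wording. No envenomation criterion, target dose or upper limit is attached, and it is not said whether the mean is over all bite victims or only those treated.

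Elsewhere the article sets a different standard:

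- The Study scheme section describes Phase IV as aiming at "optimal utilization of anti-venoms through training programs".
- The Discussion says that "severe complications can be prevented with a correct dose of anti-venom", and also that "there is a paucity of satisfactory data regarding the number of anti-venom vials needed to reverse the clinical effects of SBE".

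The article also describes too little anti-venom. The abstract's background says that "poor utilization of anti-venom results in high mortality and morbidity" (one of several causes listed there), the Introduction reports "unavailability of anti-venom and emergency ventilation services" in rural primary health centres, and the Discussion refers to "unavailability and inadequacy of anti-venom".

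Under Phase V, the impact on the healthcare system is to be "assessed by comparing prospective data with the retrospective (pre-intervention) data". Categories of envenomation by signs and symptoms appear in the Statistical analysis section as strata for the baseline data. The same section has a separate secondary outcome on the share of Medical Officers who treat according to STG 2017.

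**The concern.** The protocol's aim is correct use, but this outcome scores quantity. More vials may mean that under-treated envenomed patients now receive enough, or that patients receive more than they need. The Discussion says the number needed is poorly known, so the count has no reference value against which a rise could be judged.

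The neighbouring items help a reader but do not repair this comparison. The STG 2017 outcome counts Medical Officers, not patients or doses. The complications outcome gives clinical context but does not show whether anti-venom went to the right patients in the right amount. The envenomation strata are stated for baseline data, whereas impact rests on the before-after contrast.

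At stake is how one secondary outcome is read. A reported rise would look like improvement although the figure alone cannot say whether dosing came closer to correct.

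**Working it through.** The article gives no vial target, dose distribution, envenomed share or rate of unindicated use, so there is no figure to reproduce. All inputs below are assumptions, shown over a range. The aim is only to see whether the sign and size of the change identify better use.

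**1. Dosing among envenomed patients (applies to either denominator)**

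Set the correct dose to 1. Let f be the share of envenomed patients who are under-dosed and u their shortfall; the rest receive the correct dose. Who is treated and the envenomed share stay fixed.

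- Baseline mean = 1 − f·u.
- Good change: the under-dosed are brought up to 1. The mean becomes 1, a ratio of 1/(1 − f·u).
- Bad change: the under-dosed stay as they are and the others receive 1 + f·u/(1 − f). The mean is f(1 − u) + (1 − f) + f·u = 1, the same ratio.

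| f | u | Baseline mean | Rise in the mean, good or bad change | Over-dose of the others in the bad change |
|---|---|---|---|---|
| 0.25 | 0.20 | 0.95 | 1/0.95 = 1.053, +5% | 0.05/0.75 = 7% |
| 0.25 | 0.40 | 0.90 | 1/0.90 = 1.111, +11% | 0.10/0.75 = 13% |
| 0.50 | 0.20 | 0.90 | 1/0.90 = 1.111, +11% | 0.10/0.50 = 20% |
| 0.50 | 0.40 | 0.80 | 1/0.80 = 1.250, +25% | 0.20/0.50 = 40% |

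In each row one result describes both a success and a failure. An all-victim mean is this mean multiplied by the envenomed share, so with that share fixed the ratios are the same.

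**2. Unindicated use and case mix (only if the mean is over all bite victims)**

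Let s be the envenomed share and p = 0.20 the share of non-envenomed victims given the same number of vials as the envenomed.

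- New unindicated use: [s + (1 − s)p]/s.
- Ending unindicated use that exists at baseline: s/[s + (1 − s)p].
- Envenomed share moves by 10 percentage points, practice unchanged: (s ± 0.10)/s.

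| s | New unindicated use | Unindicated use ended | Share moves by 10 points |
|---|---|---|---|
| 0.30 | 0.44/0.30, +47% | 0.30/0.44, −32% | ±33% |
| 0.50 | 0.60/0.50, +20% | 0.50/0.60, −17% | ±20% |
| 0.70 | 0.76/0.70, +9% | 0.70/0.76, −8% | ±14% |

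On this reading poorer practice raises the mean, better targeting lowers it, and a change in who presents moves it with no change in practice. If the mean is over treated patients only, and doses are equal as assumed, every entry in this second table is 0% and only step 1 remains.

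**The case against.** The strongest reply is that the direction is reasoned. Nearly everything the article reports about supply and use points to too little anti-venom, including a study in Africa that put available effective treatments at perhaps 2.5% of need. The one irrational practice it reports is skin testing, not excess dosing. This stands: a rise is a sensible expectation here, and nothing in the article shows that over-dosing occurs. It does not make a rise interpretable once observed.

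Second, the vial count is not read in isolation. It sits beside outcomes on treatment according to STG 2017, bite-to-needle time, referral and severe complications, and training follows STG 2017. This stands in part. Those outcomes put the count in context, but none of them qualifies it by patient or by dose.

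A reader might infer that the plan would declare success from more vials alone. The text does not support that: it states no success rule resting on this outcome. A reader might also take the mean to be over all bite victims, because the referral item in the same list refers to snakebite victims. The vial item says only victims, which can equally mean those who received vials. The figures in step 2 are therefore conditional.

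Third, restricting the mean to envenomed patients would not cure the dosing ambiguity, since step 1 is computed in exactly that group. This is correct, and it is why the remedy must rest on agreement with a dosing standard and not on a narrower mean.

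**Conclusion.** The concern holds as a minor point. As worded, the outcome fixes a rise in vials as favourable, while the article's own standard is optimal use and a correct dose, and it says the dose needed is uncertain. Because the article itself sets the direction, this is more than detail left to a fuller document.

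In the assumed range, a rise of 5% to 25% in the mean is equally compatible with corrected under-dosing and with over-dosing of other patients by 7% to 40%. The larger swings from unindicated use and case mix arise only under an all-victim denominator. All of these sizes are illustrative and none estimates what the study will see.

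It would go too far to say that an increase is the wrong expectation or that the plan encourages over-use; the reported under-use makes a beneficial rise plausible. The conclusion is only that this measure alone cannot show it. One secondary outcome is affected; the primary outcomes on incidence and case fatality are not.

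**What to change.** Remove the stated increase from the outcome and compare, before and after the intervention:

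- (a) the proportion of patients with recorded envenomation whose anti-venom use agrees with STG 2017, where records allow this to be judged;
- (b) the proportion of patients without recorded signs of envenomation who received anti-venom.

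Report vials per envenomed patient by envenomation category in both periods, descriptively, without counting a rise as benefit. Item (a) is the core, because it is the only part that refers to dose. It measures agreement with the protocol's chosen guideline, which is the nearest available standard given the acknowledged lack of dosing data.

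The cost is low: a change of wording and some added analysis. According to the section on data collection tools, the retrospective and prospective forms are both to record signs and symptoms and anti-venom use. The small downside is that Phase IV trains staff to recognise the signs of envenomation, so recording may improve afterwards and shift patients between (a) and (b). That should be stated as a limitation.
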